## Abstract

**Background:**

Depression and anxiety are highly prevalent and represent a significant and well described public health burden. Whilst first line psychological treatments are effective for nearly half of attenders, there remain a substantial number of patients who do not benefit. The main objective of the present project is to establish an infrastructure platform for the identification of factors that predict lack of response to psychological treatment for depression and anxiety, in order to better target treatments as well as to support translational and experimental medicine research in mood and anxiety disorders.

**Methods/design:**

Predicting outcome following psychological therapy in IAPT (PROMPT) is a naturalistic observational project that began patient recruitment in January 2014. The project is currently taking place in Southwark Psychological Therapies Service, an Improving Access to Psychological Therapies (IAPT) service currently provided by the South London and Maudsley NHS Foundation Trust (SLaM). However, the aim is to roll-out the project across other IAPT services. Participants are approached before beginning treatment and offered a baseline interview whilst they are waiting for therapy to begin. This allows us to test for relationships between predictor variables and patient outcome measures. At the baseline interview, participants complete a diagnostic interview; are asked to give blood and hair samples for relevant biomarkers, and complete psychological and social questionnaire measures. Participants then complete their psychological therapy as offered by Southwark Psychological Therapies Service. Response to psychological therapy will be measured using standard IAPT outcome data, which are routinely collected at each appointment.

**Discussion:**

This project addresses a need to understand treatment response rates in primary care psychological therapy services for those with depression and/or anxiety. Measurement of a range of predictor variables allows for the detection of bio-psycho-social factors which may be relevant for treatment outcome. This will enable future clinical decision making to be based on the individual needs of the patient in an evidence-based manner. Moreover, the identification of individuals who fail to improve following therapy delivered by IAPT services could be utilised for the development of novel interventions.

## Background

Depression and anxiety within the general population are a continuing and significant public health problem [1]. The Adult Psychiatric Morbidity Survey showed that 16% of adults overall met the criteria for at least one common mental health disorder (defined in this survey as depression and/or anxiety disorders) [2]. Suffering from depression and/or anxiety has a significant impact on an individual’s life, including increased mortality [3], reduced quality of life [4] and reduced attendance and productivity at work [5]. The Improving Access to Psychological Therapies (IAPT) service was developed to provide psychological treatment for people with these common mental health disorders in order to address the high prevalence and burden of these disorders, and the problem that many people are untreated.

The therapeutic approaches used by IAPT are recommended as first-line treatment for mild to moderate depression and anxiety, in some cases along with appropriate medication, by the National Institute for Clinical Excellence [6]. IAPT services use a standardised protocol and collect considerable amounts of outcome data. This provides an opportunity for researchers to collect data on large populations (3000 per year in some services) of people with common mental health disorders undergoing similar treatments. Recently, the IAPT programme has reported early successes over its first three years, notably the treatment of “the first million patients” [7]. Overall recovery rates, defined as moving from caseness to non-caseness on measures of low mood and anxiety, were 45% in the last quarter of 2011/12, demonstrating consistent improvement over the duration of the programme and progression towards the original target of 50% [7].

Whilst these recovery rates are encouraging, they also show that around half of patients are not meeting standard definitions of recovery at the end of their treatments. Further, it is likely that a substantial proportion of those who do recover then go on to relapse in due course. Our knowledge of predictors of treatment response for depression and anxiety, both in terms of psychological and pharmacological treatments, is limited. It is likely that depression and anxiety disorders have many and varied causes, across psychological, social, and biological factors. Only by studying large cohorts of patients receiving treatments will it be possible to identify factors that predict positive or negative response and, by understanding these, develop new targets for treatment.

The aim of this project is therefore to provide an infrastructure to understand the predictors of treatment response, and to allow recruitment and follow up of subgroups of participants who do not respond to treatment in order to devise experimental studies to identify new treatments (both psychological and pharmacological). The project is supported by the SLaM Biomedical Research Centre which aims to provide infrastructure support for experimental medicine studies, and phase 1 and 2 trials.

### Project objectives

The objectives of the project are to:

1. Explore and describe the population attending for psychological therapy in one South London IAPT service (Southwark)

2. Embed data collection procedures within SLaM IAPT services to facilitate future research programmes

3. Collect biological samples to establish predictors of response to psychological therapy

4. Establish longitudinal predictors of response to psychological therapy

5. Identify participants for further, associated studies under the PROMPT theme

## Methods/design

### Design

This project uses a naturalistic, observational design. All eligible patients referred to Southwark Psychological Therapies Service are initially asked to consent to be contacted for research purposes, and those that agree are approached to take part in the project. Patients are approached before beginning therapy to allow collection of baseline measures and will then continue their treatment as usual within the IAPT service.

The project team carried out consultation with service users in the design of relevant materials. Firstly, the Southwark IAPT Service User Forum was consulted in two meetings about the procedure and suggested materials to be used in the project. Secondly, the FAST-R service (Feasibility and Support to Timely recruitment to Research) provided feedback and comments about the participant information sheet and consent forms used in this project.

### Ethical approval

The project has been approved by Bromley NHS Research Ethics Committee on 21^st^ October 2013 (reference: 13/LO/1347).

### Participants

Participants are recruited from one IAPT service provided by South London and Maudsley NHS Foundation Trust (SLaM). Inclusion criteria for this project are that patients are accepted by the IAPT service for treatment, and that they are able to give informed consent. Patients are excluded if they are not sufficiently fluent in English.

### Sample size

This is a naturalistic, observational project and therefore our sample size estimates are based on patient throughput and human resources. Based on these factors, we estimate to recruit up to 600 patients at baseline in the first year of the project. Using existing drop-out rates from SLaM IAPT services, we expect a drop-out rate of approximately 28%, leaving us with a sample of 472. According to power calculations, with power set at 0.8 and alpha at 0.05, this will allow us to detect standardised effect sizes of 0.13 in linear regression models estimating the effects of baseline factors in recovery. This is considered to be clinically significant; for example, a recent study of predictors of recovery [8] in the same setting showed that baseline PHQ-9 and GAD-7 scores were independently associated with recovery rates in a multiple regression model, with effect sizes ranging 0.14-0.21.

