Collecting data from participants in a naturalistic setting, whilst providing ecologically valid data, is not without its limitations. We can anticipate around 30% drop-out of patients during IAPT therapy, meaning that we will lose some final outcome data for many patients we see at baseline. However, as data is collected on every contact, with a national completion rate of 90%, this will be minimised as we will be able to use data from the final session attended. This also affords us the opportunity to investigate if there are common factors that may explain drop-out. IAPT therapy is not standardised and this will introduce variability within our sample. Patients may receive one-to-one cognitive behavioural therapy with a trained CBT therapist, or a clinical psychologist. They may also receive guided self-help with a psychological well-being practitioner. Further, patients may attend for group therapy or psycho-educational workshops. Increasingly, IAPT services are offering alternatives to CBT including but not limited to; interpersonal psychotherapy, couples therapy, and eye movement desensitization and reprocessing therapy.

IAPT services are accessed by a wide variety of patients, with a diverse range of presenting complaints. The project will initially focus its recruitment on one borough (Southwark) whose services are currently provided by South London and Maudsley NHS Foundation Trust. In terms of ethnic diversity, the Office for National Statistics reported that the population of Southwark comprises 62% from White groups, 27% from Black groups and 11% from other groups. There will also be variety in use of prescribed medication amongst the participants, and this information is not always routinely collected within IAPT services. To overcome this, participants will be asked about their prescribed medication at the research interview. However, it will not be possible to monitor any changes in dosage or medication when looking at outcomes following treatment. As part of the standard IAPT data collection, participants are asked if they are prescribed medication, and if they are currently taking their medication. It is possible that a participant may change dose or even drug whilst receiving therapy.

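### The analysable sample of 472 does not follow from 600 recruits and about 28% drop-out, which leaves 432; the effect on the power statement is small

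*Protocol article*

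**What the plan says.** The Sample size section of the protocol article bases its numbers on patient throughput and staffing. It gives a recruitment figure: "we estimate to recruit up to 600 patients at baseline in the first year of the project". It then applies attrition taken from existing service data: "we expect a drop-out rate of approximately 28%, leaving us with a sample of 472". The power statement follows directly. "with power set at 0.8 and alpha at 0.05", the resulting sample is said to allow the study to "detect standardised effect sizes of 0.13 in linear regression models". The section judges this effect clinically significant by comparison with an earlier study in the same setting, "with effect sizes ranging 0.14-0.21".

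The Discussion returns to attrition among the limitations: "We can anticipate around 30% drop-out of patients during IAPT therapy". It adds that the loss of outcome data can be limited: "this will be minimised as we will be able to use data from the final session attended".

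**The concern.** The recruitment figure, the drop-out rate and the remaining sample are given together in the Sample size section, and the third should be the product of the first two. It is not. The figure of 472 is the only analysis sample size in the article, and the power statement is worded as a consequence of it. A reader, or a later report of the study, may take 472 as the planned number and 80% power at 0.13 as established from it. What is at stake is whether the published sample size agrees with its own inputs, and whether the detectable effect still holds once it does.

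**Working it through.** **Inputs, all from the Sample size section:** recruits N = 600; drop-out d = 0.28; stated remaining sample 472; power 0.80; alpha 0.05; detectable standardised effect 0.13; comparison effects 0.14 to 0.21.

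**Assumptions:** the section gives neither the sidedness of the test nor the exact effect measure. I take a two-sided test and read 0.13 as the standardised slope (equivalently the correlation) for a single predictor.

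**Step 1, attrition.** Remaining sample = N × (1 − d).
- 600 × (1 − 0.28) = 600 × 0.72 = **432**. The stated 472 is 40 higher (40/432 = 9%).
- Drop-out implied by 472: 1 − 472/600 = 0.213, or 21.3%.
- Recruits implied by 472 at 28% drop-out: 472/0.72 = 655.6, so 656.
- Rounding of the rate does not help: 27.5% gives 435 and 28.5% gives 429.
- Dividing by 1 + d, a common slip, gives 600/1.28 = 469. This is close to 472 but not equal to it, and nothing in the article shows that it was done.

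**Step 2, the plan's own detectable effect from 472.** With the Fisher z approximation, the smallest detectable correlation is tanh[(1.960 + 0.842)/√(n − 3)], and power at r is Φ[atanh(r) × √(n − 3) − 1.960].
- n = 472: tanh(2.802/√469) = tanh(0.1294) = 0.129. Power at 0.13 = Φ(0.1307 × 21.66 − 1.960) = Φ(0.871) = 0.808.

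The published 0.13 is therefore reproduced from 472. A one-sided test with 472 would give 0.114, which supports the two-sided assumption.

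**Step 3, the same calculation with 432.**
- n = 432: tanh(2.802/√429) = tanh(0.1353) = 0.134. Power at 0.13 = Φ(0.1307 × 20.71 − 1.960) = Φ(0.748) = 0.773.

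**Step 4, check by other methods** (two-sided 0.05).

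| Method | Detectable effect, n = 472 | Detectable effect, n = 432 | Power at 0.13, n = 472 | Power at 0.13, n = 432 |
|---|---|---|---|---|
| Fisher z, correlation | 0.1286 | 0.1344 | 0.808 | 0.773 |
| Noncentral F, r | 0.1282 | 0.1339 | 0.811 | 0.776 |
| Noncentral F, effect size f | 0.1292 | 0.1351 | 0.805 | 0.769 |
| Slope, 2.802/√n | 0.1290 | 0.1348 | not computed | not computed |

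Read as a correlation or slope, the result for 432 rounds to 0.13. Read as f, it is 0.1351 and just rounds to 0.14. On every reading it stays below 0.14 before rounding.

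**Step 5, number needed.** By Fisher z, 80% power at exactly 0.13 needs (2.802/0.1307)² + 3 = 462.2, so 463 patients. The stated 472 clears this and 432 does not.

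**Step 6, the cited range.** With n = 432, power at 0.14, the lower end of the cited effects, is Φ(0.1409 × 20.71 − 1.960) = Φ(0.959) = 0.83.

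**The case against.** The strongest reply is that the power claim largely survives. The effect is published to two decimals, and 432 patients also give 0.13 at that precision under the slope or correlation reading. For the same reason, it cannot be shown that the calculation was run on 472: a one-digit slip for 432, with the power calculated on 432, fits the published 0.13 equally well. Both points stand. They limit the consequence but leave the attrition figure wrong.

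A second reply is that patients who drop out can still contribute an outcome, since the Discussion plans to use the last session attended. The analysable number could then exceed 432. To reach 472, 40 of the 168 expected drop-outs (600 × 0.28), or 24%, would need a usable outcome. That is possible, but the Sample size section presents 472 as what remains after 28% drop-out and makes no such argument. This does not rescue the sentence as written.

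A reader might also infer that 432 is a best case because 600 is worded as a maximum. The article does not support this: 600 is an estimate for the first year only, extension to other services is planned, and last-session data may add outcomes.

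Nor are the two drop-out figures in conflict. Approximately 28% and around 30% are compatible roundings. Taken literally, 30% would leave 420, which is further from 472.

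**Conclusion.** The error is real and minor. On the section's own inputs the remaining sample is 432, which is 40 fewer than stated. Under a two-sided 0.05 test of one standardised slope, the detectable effect at 80% power moves from about 0.129 to about 0.134, and power at exactly 0.13 moves from about 0.81 to 0.77–0.78.

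It is tempting to conclude that the power claim fails. That follows only if 0.13 is taken as exactly 0.130; at the published precision the claim holds under the assumed effect measure. The comparison with cited effects of 0.14 to 0.21 is not overturned, although the margin at the lower end narrows. Recruitment was set by throughput and staffing, so no design decision depends on the difference.

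The article does not show which of 600, 28% and 472 is the wrong figure, so it cannot be said that 472 is the one that slipped.

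**What to change.** Reconcile the three figures in the Sample size section.

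- If 600 and 28% are right, state the remaining sample as 432 and the detectable effect as about 0.134 at 80% power (power at exactly 0.13 about 0.77 to 0.78).
- If 472 rests on another recruitment or drop-out figure, or on counting last-session outcomes from patients who drop out, state that basis and the number it yields.
- In either case, name the sidedness and the effect measure so that the calculation can be repeated.

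The cost is a change to one or two sentences. Design, recruitment and analysis are untouched, and the stated detectable effect becomes at most slightly less favourable.

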### Analysis

Descriptive summaries of socio-demographic information will be provided for baseline, and follow up time-points for the sample as appropriate. Descriptive summaries at the level of IAPT services will also be provided. Missing data will be reported for all treatment time-points to describe retention/drop-out rates. Reasons for drop-out will be recorded. We will use the STROBE statement (http://www.strobe-statement.org/index.php?id = available-checklists) for a list of items to be reported. All statistical analyses will be carried out in the statistical software package STATA. Descriptive summaries for all outcome measures will be provided. Continuous outcome measures will be inspected visually to assess the normality of data and to check for outliers. Univariate associations with IAPT non-recovery will be explored using t-tests (for normally distributed data) and Mann-Whitney tests (for skewed data). The independence of associations between the proposed predictor variables and IAPT non-response will be explored using linear mixed model methods (for continuous outcome measures) and logistic regression (for categorically-defined outcomes i.e. recovered vs. non-recovered). The possibility of sex interactions and non-linear effects will be examined. Analysis of residuals from the model will be performed to assess the model fit and to check for outliers.

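### The only detectable effect stated, 0.13, is for linear regression, but recovery is to be analysed by adjusted logistic regression, for which 0.13 is not shown to hold

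*Protocol article*

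**What the plan says.** In the protocol article, the Sample size section bases recruitment on throughput and staffing: "we estimate to recruit up to 600 patients at baseline in the first year of the project". It continues: "we expect a drop-out rate of approximately 28%, leaving us with a sample of 472". Then, "with power set at 0.8 and alpha at 0.05", it reports that "this will allow us to detect standardised effect sizes of 0.13 in linear regression models estimating the effects of baseline factors in recovery". To argue that this effect matters clinically, it cites an earlier study in the same setting, where baseline PHQ-9 and GAD-7 scores "were independently associated with recovery rates in a multiple regression model, with effect sizes ranging 0.14-0.21".

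The Outcome measures section makes symptom change on the two scales the primary outcome. It also defines a non-recovered group: patients who meet caseness on both scales at their last appointment. The Analysis section uses linear mixed models for continuous outcomes and "logistic regression (for categorically-defined outcomes i.e. recovered vs. non-recovered" for the binary ones. For both, the aim is to find which predictors are independently associated with outcome. Table 2 lists 15 measures in 14 domains, and Table 1 adds eight demographic and treatment factors.

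**The concern.** The power statement names recovery as the outcome and linear regression as the model. The plan's own model for recovery is logistic. Its detectable effect is naturally an odds ratio, and depends on the outcome rate and on how much of a predictor's variance is shared with the others. The Sample size section gives neither, and does not define its standardised effect. A reader planning from the article, or later interpreting a null result for a predictor of recovery, would take 0.13 as the sensitivity of that analysis when it has not been shown for it. Setting 0.13 beside 0.14 to 0.21 adds to this, since the scale of neither figure is given.

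**Working it through.** **Inputs**

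- Power 0.80 and alpha 0.05 (Sample size). Sidedness is not stated; two-sided is assumed, so the sum of normal quantiles is 1.960 + 0.842 = 2.802.
- n = 472 as printed. The section's own drop-out gives 600 × 0.72 = 432; 472/600 = 0.787 would mean 21.3% drop-out.
- Outcome rate: none in the power statement. The Background gives 45% recovered nationally. I use 45%, with 30% as an assumed alternative.
- R² of a predictor on the other predictors: not in the document. Assumed values 0, 0.2 and 0.3.

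**1. Reproducing 0.13.** For one correlation or standardised slope, r = tanh(2.802/√(n − 3)).

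- n = 472: 2.802/√469 = 0.1294, so r = 0.129. The exact F test gives 0.128.
- As a partial correlation in a model with 15 to 25 predictors, the exact F test still gives 0.128.
- A one-sided test would give 0.114, which does not match.

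The printed figure is therefore sound for a two-sided linear test at n = 472.

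**2. The linear figure at n = 432.** 2.802/√429 = 0.1353, so r = 0.134. Power for 0.13 is Φ(0.13 × √432 − 1.960) = Φ(0.742) = 0.77.

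**3. The planned recovery model.** For logistic regression, the detectable log odds ratio per SD is 2.802/√(n·p(1 − p)(1 − R²)). For n = 432, p = 0.45 and R² = 0: 432 × 0.45 × 0.55 = 106.92, its root is 10.34, 2.802/10.34 = 0.271, and exp(0.271) = 1.31. In the same way:

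| n | Outcome rate | R² (assumed) | Log OR per SD | OR per SD |
|---|---|---|---|---|
| 472 | 45% | 0 | 0.259 | 1.30 |
| 432 | 45% | 0 | 0.271 | 1.31 |
| 432 | 30% | 0 | 0.294 | 1.34 |
| 432 | 45% | 0.2 | 0.303 | 1.35 |
| 432 | 45% | 0.3 | 0.324 | 1.38 |

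**4. Does the OR correspond to 0.13?** That depends on the scale. Take n = 472, 45%, no overlap, log OR 0.259.

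- Observed scale (correlation with the binary outcome): 0.259 × √(0.45 × 0.55) = 0.129, essentially the printed value.
- Underlying continuous scale with a logistic distribution: 0.259/√(0.259² + π²/3) = 0.141.

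Power for an effect of 0.13, at a 45% rate and with no overlap, follows the same split:

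| Scale on which 0.13 is read | n = 472 | n = 432 |
|---|---|---|
| Observed binary outcome | 81% | 77% |
| Underlying variable, logistic | 73% | 69% |
| Underlying variable, normal | 61% | 58% |

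The article does not say which row applies.

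**The case against.** The strongest reply is that little is wrong. The primary outcome is symptom change, continuous outcomes go to linear models, and a linear power statement fits that part of the plan. On the observed scale, logistic regression at a rate near 45% costs almost nothing (0.129 against 0.13). Recruitment rests on throughput, so no design decision depends on the figure. A condensed article may also leave logistic effect sizes to the full plan. All of this limits the size of the point. It does not remove the mismatch, because the article does state a detectable effect and attaches it to recovery under a model not planned for that outcome.

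A reader might go on to infer four stronger things that the document does not support:

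- **That 0.13 is for a single predictor only.** The text speaks of models and baseline factors in the plural, and the same value results for a partial correlation with many covariates.
- **That power for recovery is 58% rather than 80%.** That value needs both n = 432 and a normally distributed underlying variable; other admissible readings give 69% to 81%.
- **That overlap lifts the detectable linear coefficient to 0.15 to 0.19.** This needs an R-squared that the article does not give, and it ignores the fall in residual variance that adjustment also brings.
- **That the study cannot reach the lower end of the 0.14 to 0.21 benchmark, or compares itself with the wrong quantity.** The cited study's metric is not given. The benchmark comes from a multiple regression on recovery rates, so it may already be adjusted and on a recovery scale. The article cites it to show that 0.13 is clinically significant.

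**Conclusion.** The point holds as a mismatch between the power statement and the planned analysis of recovery. The figure 0.13 is valid for a linear test at n = 472 and is not shown for the adjusted logistic model. For that model, the detectable odds ratio per SD at n = 432 is about 1.31 with a 45% rate and no overlap, 1.34 at 30%, and 1.35 to 1.38 at 45% with R-squared 0.2 to 0.3.

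These values rest on a two-sided test, on the 28% drop-out taken at face value, and on outcome rates and overlaps that are assumed. The 45% is a national rate of moving out of caseness, whereas this project counts as non-recovered only those meeting caseness on both scales, so the rate here may differ. The Discussion also plans to use the last attended session for patients who drop out, so the analysed number could exceed 432. The size of any power loss stays open until the effect scale, outcome rate and overlap are stated.

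**What to change.** In the Sample size section:

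1. Attach the linear figure to continuous symptom change, and restate it at the n that 28% drop-out from 600 gives: about 0.134 at n = 432, with about 77% power for 0.13. If 472 is the intended number, correct the drop-out rate instead.
2. For recovered versus non-recovered, give a detectable odds ratio per SD, with the assumed outcome rate and the assumed R-squared with the other predictors. The values in the verdict can serve as the range.
3. Say on which scale 0.13 and the 0.14 to 0.21 benchmark are expressed before setting them side by side.

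The cost is a few restated sentences. Recruitment, data collection and the analysis models stay as they are.
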